Unit of randomisation: Middle layer super output areas (MSOAs) within Birmingham and the Black Country will serve as the units of randomisation (clusters) and will be randomly allocated on a 1:1 basis to receive the intervention or control. Each MSOA represents a geographically defined area with a population of approximately 5000–15 000 residents, providing an appropriate ecological unit for community engagement and potential linkage with routinely collected data in future phases.

Within each selected MSOA, the intervention will be implemented in community settings such as places of worship (eg, Black-majority churches), youth centres, community centres and youth residential settings that already serve local Black communities. To ensure feasibility and representativeness, we restricted the sampling frame for cluster randomisation to MSOAs with intermediate Black population density, based on the proportion of residents identifying as Black (African, Caribbean or Black British) in the 2021 Census. This restriction avoids areas where community engagement would be unfeasible (very low-density MSOAs) and reserves very high-density MSOAs for the future definitive trial. Importantly, if recruitment and delivery are feasible in intermediate-density MSOAs, it is likely to remain feasible in MSOAs with higher Black population density, providing a conservative test of feasibility.

Randomisation will use restricted (covariate-constrained) allocation to maintain approximate balance on (i) area-level deprivation and (ii) anticipated participant numbers (based on venue capacity and local population). The randomisation sequence will be generated by an independent researcher/statistician prior to implementation.

By design, concealing treatment allocation is not possible in this community-based feasibility study. Given the nature of the training intervention, blinding of participants and researchers is not feasible. However, the primary feasibility outcomes (recruitment and retention rates, measure completion and acceptability) are objective and unlikely to be influenced by allocation awareness.

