Sample size: We will recruit 120 participants from the eight randomised clusters. Formal power calculations are not necessary as no hypothesis testing for trial effectiveness is being evaluated.^55^ A sample of 120 (with ~60 per arm) meets sample size recommendations for pilot and feasibility studies and is sufficient to provide precision of feasibility parameters and estimates of study summary measures for a definitive trial.^56^ 20 participants in total will be recruited for focus groups (three groups of five diverse participants) and five 1:1 interviews.

Analysis: Descriptive statistics will be used to assess training fidelity and feasibility outcomes. Other data will be analysed using thematic analysis to generate important themes and patterns.^57 58^ For the secondary outcomes, means, CIs, intra-cluster correlation coefficient (ICC) of the outcome measures (both within-study and between-study clusters) will be estimated to determine which outcome(s) are most sensitive to change and provide sample size calculation for definitive trial.

ICCs for each quantitative outcome will be estimated using mixed-effects regression models including a random intercept for clusters, following the approach recommended by Hemming *et al* for cluster and stepped-wedge feasibility studies.^59^ Analyses will be undertaken in Stata (V.18). The ICC estimates, along with observed variances and completion rates, will inform the design of the definitive trial by (i) identifying outcomes that are most sensitive to change and (ii) providing parameter estimates for sample size and power calculations.

Missing data will be assessed for extent and pattern. The proportion of missing values for each variable will be reported, and exploratory analyses will assess whether missingness appears random or systematic. As this is a feasibility study, no formal imputation will be undertaken for primary feasibility outcomes; however, simple sensitivity analyses using mean or regression-based imputation may be conducted to evaluate the potential impact of missing data on secondary outcomes.^55 56^ The findings will inform strategies for minimising and handling missing data in the future definitive trial.

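### WP1's optional imputation check for missing secondary-outcome scores would show the effect of the imputation method, not of the missing data

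*Protocol article*

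**What the plan says.** In the Analysis paragraphs of WP1 (Protocol article), missing data are first to be described: the proportion missing for each variable, and whether missingness looks random or systematic. Then "no formal imputation will be undertaken for primary feasibility outcomes", but for the secondary outcomes "simple sensitivity analyses using mean or regression-based imputation may be conducted to evaluate the potential impact of missing data on secondary outcomes". The secondary outcomes are the knowledge, stigma and help-seeking scales.

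The main analysis is separate from this check: "ICCs for each quantitative outcome will be estimated using mixed-effects regression models including a random intercept for clusters". On what goes forward, the section says "The ICC estimates, along with observed variances and completion rates, will inform the design of the definitive trial", one aim being "providing parameter estimates for sample size and power calculations".

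**The concern.** A sensitivity analysis helps only if a change in the result can be attributed to the thing being varied. Filling gaps with a mean, or with a fitted value that carries no residual, adds scores with too little spread. The variance therefore shrinks even when missingness is harmless and the observed-data analysis is unbiased. The ICC may also move, in a direction set by a choice the protocol leaves open: overall mean or cluster mean, and regression with or without cluster.

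Two misreadings could follow. A difference from the main analysis could be taken as evidence that missing data matter, when the imputation produced it. Similar means could be taken as reassurance, although neither named method examines departure from missing at random. That departure is the live question, since the same paragraph plans to ask whether missingness is systematic. The section also says that the findings will guide missing-data handling in the definitive trial, so a weak method could be inherited.

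**Working it through.** **Inputs from the protocol.** 120 participants, 8 clusters, 1:1 allocation. These agree: 120/2 = 60 per arm and 120/8 = 15 per cluster. No dropout rate, SD, ICC, alpha or power is given ("Formal power calculations are not necessary as no hypothesis testing for trial effectiveness is being evaluated"), so there is no planned figure to reproduce.

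**Assumptions.** Missing completely at random at 10%, 20% or 30%; true ICC 0.02, 0.05 or 0.10; within-cluster baseline to follow-up correlation r = 0.5; true variance 1; no treatment effect.

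**Step 1, algebra.** With a fraction m missing, overall-mean imputation leaves a variance of about 1 − m: 0.90, 0.80 and 0.70 for m = 0.10, 0.20 and 0.30. Deterministic regression on baseline leaves about 1 − m(1 − r²). For m = 0.20 this is 1 − 0.20 × 0.75 = 0.85.

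**Step 2, simulation.** 8 clusters of 15, 4,000 runs, true ICC 0.05, 20% missing. The last column is V × (1 + 14 × ICC), the factor to which a cluster trial's sample size is proportional. It borrows the pilot's 15 per cluster, because no Phase 3 cluster size is given.

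| Handling | Variance V | ICC | V × (1 + 14 × ICC) |
|---|---|---|---|
| Full data | 1.000 | 0.052 | 1.73 |
| Observed data only | 0.999 | 0.053 | 1.74 |
| Overall mean | 0.797 | 0.043 | 1.28 |
| Cluster mean | 0.827 | 0.101 | 2.00 |
| Regression on baseline | 0.854 | 0.051 | 1.46 |
| Regression on baseline and cluster | 0.872 | 0.087 | 1.93 |
| Baseline regression plus random residuals, no cluster term | 1.000 | 0.043 | 1.60 |

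The observed-data row is essentially unbiased. The last row shows that residual draws alone are not enough: the variance recovers, but the ICC still falls because the cluster structure is missing from the imputation.

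**Step 3, range over all scenarios.**
- Overall mean: variance down 10–30%, ICC down about 10–30%.
- Cluster mean: variance down about 8–26%, ICC up from about 1.2-fold to about 5-fold.
- Regression on baseline: variance down about 7–22%, ICC changed by at most about 6%.
- Regression on baseline and cluster: variance down about 6–19%, ICC up about 1.2- to 3.7-fold.

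**Step 4, confidence intervals.** For an overall mean, SE² is about V × (1 + (c − 1) × ICC)/N, with c scores per cluster.
- Observed data (N = 96, c = 12): 0.999 × (1 + 11 × 0.053)/96 = 0.0165.
- Overall mean (N = 120, c = 15): 0.797 × 1.602/120 = 0.0106. Relative width is √(0.0106/0.0165) = 0.80.
- Cluster mean: 0.827 × 2.414/120 = 0.0166. Relative width is about 1.00.
- Cluster mean, interval ignoring clustering: √[(0.827/120)/(0.999/96)] = 0.81.

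Overall-mean imputation thus narrows the interval by about a fifth. Cluster-mean imputation does so only if the interval ignores clustering.

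**Step 5, if imputed figures were carried to Phase 3.** Against 1.73 for full data, the overall mean gives 1.28/1.73 = 0.74 (too small). Regression on baseline gives 1.46/1.73 = 0.85 (too small). The cluster mean gives 2.00/1.73 = 1.16 (too large), and regression on baseline and cluster gives 1.93/1.73 = 1.12 (too large).

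**The case against.** The strongest reply is that nothing important depends on this check. It is optional, no effectiveness hypothesis is tested, and Phase 3 is to be informed by mixed-model ICCs and observed, not imputed, variances. That stands, and it limits the point to a side analysis.

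A reader might infer more: that the pilot's inputs to Phase 3 are corrupted and the definitive trial will be underpowered. Sizing on a variance of 0.80, for example, would turn a planned 90% power into Φ(3.242 × √0.8 − 1.96) = 0.83. The documents do not support this. It needs someone to carry the imputed variance forward, which the protocol does not plan, and it ignores the design effect. Step 5 shows that cluster-based imputation would make the trial too large.

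Nor do the variance and ICC make up the pilot's main purpose. The Phase 2 aims and the WP1 objective put feasibility and acceptability first, and completion rates are passed on beside the ICC and variance.

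Two further replies stand in part. The protocol does not say that the regression imputation is single or deterministic; the word for simple makes that a fair reading, but it remains an inference. Regression on baseline alone leaves the ICC nearly unchanged, so there is no blanket ICC claim. Eight clusters also estimate the ICC poorly in any case: its simulated standard deviation with observed data was 0.067, more than the assumed ICC itself.

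The detail of an imputation model may be left to an analysis plan. Here, however, the article names the methods, and mean imputation is unsuitable for this purpose however it is specified.

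**Conclusion.** The point holds in limited form, and its severity is minor. As worded, the optional check cannot show how missing data affect the secondary-outcome variances, ICCs and confidence intervals. At an assumed 20% missing and ICC 0.05, the named methods give 0.80 to 0.87 of the true variance and an ICC between about 0.043 and 0.101, when there is no bias to detect. For regression-based imputation this assumes no residual draws. The figures rest on assumed missingness, ICC and baseline correlation, none of which the protocol states.

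The planned Phase 3 inputs are sound in these scenarios. They would be affected only if imputed figures were carried forward, and the size and direction of the error would then depend on the imputation used.

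**What to change.** Replace the sentence on imputation with text to this effect: secondary outcomes are analysed by a mixed model using all available T0 and T1 scores, with terms for cluster and for repeated scores on a participant. This model is the only source of the variance and ICC passed to Phase 3. Any sensitivity analysis uses multiple imputation with residual draws and with baseline, arm and cluster in the imputation model. A simple delta shift by arm in the imputed scores then examines departure from missing at random, over a range that the sponsor justifies. Mean imputation and deterministic regression imputation are not used.

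The cost is one changed sentence and a few lines of Stata, with no effect on recruitment or participants. The downside is a little more analysis work, and imputation models with only eight clusters will be imprecise.

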#### WP2: a pilot SWCRT of e-learning for mental health professionals

Research question: Is an e-learning module on culturally responsive care feasible and acceptable for delivery to NHS mental health professionals?

Design: Pilot stepped-wedge cluster randomised trial assessing feasibility, uptake and change in multicultural competence scores.

Aims and objectives: To evaluate the feasibility and acceptability of the e-learning to inform our implementation evaluation in a future trial (phase 3).

Design: We will adopt a pragmatic SWCRT^60^ design with random and sequential crossover of clusters (youth mental health teams) from control to intervention (our e-learning module) until all clusters are exposed. Because training is delivered openly within existing clinical teams, outcome assessment cannot be blinded; feasibility endpoints are objective and carry minimal risk of bias.

Methods: There will be a phased and sequential implementation of the e-learning at regular intervals across teams and trusts over a 6-month period (months 4–9; figure 3). Staff will complete the training outcome measure before and after the e-learning.

**Figure 3 F3:**
[figure not shown]
Co-STARS e-learning stepped-wedge rollout. This schematic shows the sequential rollout of the e-learning intervention across six clusters over the 12-month study period. *Forward Thinking Birmingham of Birmingham Women’s and Children’s NHS Foundation Trust (FTB of BWC NHS FT). **Early Intervention Services of Black Country Healthcare Foundation Trust (EIS of BCH NHS FT).

The training will be deployed in a staggered manner in line with the stepped wedge approach. Starting in the first Mental Health Trust (Forward Thinking Birmingham (FTB) of Birmingham Women’s and Children’s NHS Foundation Trust; please see setting for description) in month 4 and rolled out to the four teams in staggered intervals. The training will then be rolled out in the second Mental Health trust (Early Intervention Services (EIS) of Black Country Healthcare NHS Foundation Trust) with staggered implementation between months 6–9. Through the course of implementation, we will conduct staff focus groups and semi-structured interviews. Baseline (pre-training) and post-training (4 weeks later) data will be collected electronically via the NHS Learning Hub platform.

Setting: FTB, part of the Birmingham Women’s and Children’s NHS Foundation Trust, is a 0–25 years community and inpatient mental health service and is the primary mental health service regionally for this population. Within FTB, there are four specialised care pathways, including Youth Justice, Specialist Eating Disorders and Core mental health team and EIS, which offer intensive community support to young people with a FEP.

The second trust is Black Country Healthcare NHS Foundation Trust, in which we will target four EIS teams (Dudley, Walsall, Sandwell and Wolverhampton), which provides community support to young people with psychosis between the ages of 14 and 65 years.

Randomisation: Cross-over of clusters (clinical team; n=6) from control to intervention will occur approximately every 4 weeks.

Population: *Inclusion criteria*: NHS staff working within participating teams. *Exclusion criteria:* administrative personnel not directly engaged in mental healthcare delivery. Recruitment will occur via internal staff communications and service managers. A range of professionals (n=120) will be expected to complete the training, including psychiatrists, psychologists, community psychiatric nurses, occupational therapists, support workers and social workers. A purposive sampling method will be used to recruit staff to the focus groups and 1:1 interview, ensuring a balance of staff backgrounds, experience and representation from across different teams and trusts. We will also adhere to INCLUDE guidelines to ensure diversity and inclusion in our sampling.^61^

Intervention: The intervention is a 60 min e-learning module targeted at professional systems and public organisations involved in mental healthcare pathways. This e-learning is hosted by the NHS Learning Hub platform. Informed by lived experience, the e-learning seeks to raise awareness of sociocultural diversities, awareness of cultural barriers, multicultural knowledge and sensitivity and responsiveness to patients from Black ethno-racial backgrounds.

Control: The control condition will be the unexposed observation period before sequentially crossing over to the exposed observation period (receiving the intervention).

Outcome: Feasibility process outcomes will include training uptake, defined as the proportion of eligible staff completing the e-learning module within each cluster, and acceptability, assessed quantitatively through completion and satisfaction rates and qualitatively via staff focus groups and interviews exploring the training’s perceived relevance, usefulness and delivery.^62^ The qualitative component will be guided by the Acceptability of Intervention Measure framework. Secondary outcome will be assessed using the California Brief Multicultural Competence Scale (CBMCS),^63 64^ which assesses mental health staff knowledge, attitudes, skills and competencies when working with minoritised groups. The CBMCS has shown strong reliability (Cronbach’s α=0.91) and construct validity across diverse healthcare professional samples.^63 64^ Pre-training and post-training CBMCS scores will be compared at individual and cluster levels to estimate mean change and ICCs.

Sample size: Formal power calculations are not necessary as no hypothesis testing for trial effectiveness is being evaluated.^55^ A sample of 120 meets sample size recommendations for pilot and feasibility studies and is sufficient to provide precision of feasibility parameters and estimates of study summary measures for a definitive trial.^56^

Analysis: Descriptive statistics will summarise training uptake, completion rates and acceptability indicators for each cluster and step period. Quantitative comparisons of pre-training and post-training CBMCS scores will be undertaken using mixed-effects linear regression models with a random intercept for cluster and a fixed effect for time step, following Hemming *et al*’s recommendations for stepped-wedge feasibility trials. Analyses will be performed using Stata (V.18).

Qualitative acceptability data will be analysed thematically to identify perceived enablers and barriers to implementation.

Estimates of outcome variability, ICCs and temporal trends will be reported with 95% CIs to inform sample size and power calculations for the definitive trial.

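### WP2 promises random crossover of teams but orders the rollout by trust, so part of any trust difference in CBMCS enters the modelled training effect and time trend

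*Protocol article*

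**What the plan says.** All of this is in the WP2 section of the protocol article.

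- **Design:** "random and sequential crossover of clusters (youth mental health teams) from control to intervention".
- **Rollout text under Figure 3:** the training starts in FTB "in month 4 and rolled out to the four teams in staggered intervals". Then: "The training will then be rolled out in the second Mental Health trust", "with staggered implementation between months 6–9".
- **Randomisation:** "Cross-over of clusters (clinical team; n=6) from control to intervention will occur approximately every 4 weeks". The item does not say what is randomised, or whether order is random within or across trusts.
- **Setting:** FTB is a 0–25 years service with four pathways, one of them EIS. In the second trust, "we will target four EIS teams (Dudley, Walsall, Sandwell and Wolverhampton" are named, and these serve ages 14 to 65.
- **Measurement:** "Baseline (pre-training) and post-training (4 weeks later) data will be collected electronically via the NHS Learning Hub platform".
- **Analysis:** pre- and post-training CBMCS scores are compared by "mixed-effects linear regression models with a random intercept for cluster and a fixed effect for time step". Outcome variability, ICCs and temporal trends are to be reported with 95% CIs for planning the definitive trial.

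**The concern.** A stepped-wedge design separates the effect of training from calendar time because chance decides which clusters cross over early. If the first trust always starts before the second, chance decides at most the order within each trust, and early and late steps are populated largely by different trusts. The model then has to estimate time steps and the training effect from data in which trust and time move together. It can separate them from a trust difference only through the random cluster intercept.

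At stake are the model-based CBMCS training estimate and the temporal trends, which are inputs to the definitive trial. The description of the allocation is also at stake: the Methods and analysis section gives feasibility of randomisation as one reason for a randomised pilot.

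**Working it through.** The article gives no WP2 calculation to reproduce, so I worked out how much of a constant trust difference d (FTB minus second trust, in CBMCS SD units) passes into the training estimate under the stated model.

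**From the article:** 120 staff, six clusters, one crossover about every 4 weeks, FTB's four teams from month 4, second trust in months 6–9, cluster intercept plus time step.

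**Assumed:** total SD 1; staff split equally (20 per team, or 15 with eight teams); ICC 0.01–0.20; within-person correlation 0–0.9. The 4+2 split between trusts is also assumed. The article names four plus four teams but n=6, a separate inconsistency.

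**Association of trust with step.** The correlation between trust and start step is 0.83 in size for strict 4+2 order, 0.67 for eight teams with overlap, and 0.60 for six teams with the second trust starting in months 6 and 9. A fully random order of 4+2 teams puts all FTB teams first with probability 1/15 = 6.7% (48 of 720 orders).

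**Strict 4+2 order, pre/post data only.** Teams 1–6 start at steps 1–6, each measured once before and once after. Each of periods 1–5 then holds one trained team (team p) and one untrained team (team p+1). The first and last periods hold one team each and are absorbed by their time effects. The training estimate is a weighted mean of five between-team contrasts. Contrasts 1–3 are FTB against FTB, contrast 4 is FTB against the second trust, and contrast 5 is within the second trust. The share of d that leaks in is the weight on contrast 4.

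At ICC 0.05 and correlation 0.7:

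- Variance of a team mean: 0.05 + 0.95/20 = 0.0975. Pre/post covariance: 0.05 + 0.95×0.7/20 = 0.08325.
- Contrast variance: 2×0.0975 = 0.195. Neighbouring contrasts share a team, so their correlation is −0.08325/0.195 = −0.427.
- GLS weights are proportional to 2.746, 4.091, 4.493, 4.091, 2.746 (sum 18.166).
- Leak: 4.091/18.166 = **0.225**. SE: √(0.195/18.166) = **0.104**.
- With a trust term, contrast 4 drops out and the leak is 0. The remaining weights are 2.246 + 2.917 + 2.246 + 1 = 8.408, so the SE is √(0.195/8.408) = **0.152**.

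Over ICC 0.01–0.20 and correlation 0–0.9 the leak stays at 0.21–0.23. Over all 15 possible trust orders it runs from −0.225 to +0.225 with mean 0, so the strict order is an extreme one.

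**Other layouts, same GLS method:**

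| Layout | Data | Leak (share of d) |
|---|---|---|
| Eight teams, months 4–7 and 6–9 | pre/post | 0.21–0.22 |
| Six teams, FTB months 4–7, second trust in any two of months 6–9 | pre/post, ICC 0.05, correlation 0.7 | 0.07 (months 6 and 9) to 0.25 (months 7 and 8) |
| Strict 4+2 | every step, correlation 0 | 0.38, 0.13, 0.07, 0.03 at ICC 0.01, 0.05, 0.10, 0.20 |
| Strict 4+2 | every step, correlation 0.7 | 0.05, 0.03, 0.02, 0.01 at the same ICCs |

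The layout with months 6 and 9 falls to about 0.02 at ICC 0.01 with correlation 0.

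**Time trend.** In the strict pre/post layout (ICC 0.05, correlation 0.7) the fitted period effects absorb 1.17 d in the first period and −0.18 d in the last, a spurious drift of 1.17 + 0.18 = 1.35 d. With every team measured at every step, the drift is only about 0.03 d.

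**The case against.** Several points limit the concern, and most of them stand.

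- **Randomisation is not shown to be absent.** A reader might infer that the claim of random crossover is false. The text neither states nor excludes random order within trust, which would still be a random crossover. What is shown is an unreconciled description.
- **The trusts are not cleanly separated.** A reader might infer that every FTB team starts before any team in the second trust, or that early comparisons set trained FTB teams against untrained second-trust teams. Four FTB teams at 4-week steps from month 4 run to about month 7, while the second trust starts in months 6–9. Even under strict order with pre/post data, the two trusts meet in one period only. Figure 3 would show the actual order but is not available here.
- **No trust difference is documented.** The contrasts in the Setting item concern patients and pathways, whereas CBMCS measures staff, and FTB has its own EIS pathway. A large assumed gap also sits badly with a small ICC. A 0.5 SD gap over a 4:2 split adds 0.25×(2/3)×(1/3) = 0.056 to the between-team variance, more than the whole 0.05. The gap to expect from chance team differences at ICC 0.05 is about √0.05×√(1/4+1/2) = 0.19 SD. The bias is then about 0.225×0.19 = 0.04 SD, or 0.4 of the SE of 0.104.
- **The model statement is condensed.** A statistical analysis plan may add a trust term, so its absence from one sentence is not a fault in itself.
- **CBMCS is secondary** and no effectiveness test is planned. A constant trust difference cancels from simple within-team mean change.

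None of this reconciles the Design item with the rollout text, and the model as written leaves the trust difference in.

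**Conclusion.** The point holds as a should-fix. As described, order is random at most within trust, trust is strongly associated with step, and the stated CBMCS model lets part of any constant trust difference into the training estimate. The share is fairly stable at about 0.22 for pre/post data under strict order or with eight teams. It is less certain with six overlapping teams, and with complete data it depends on the ICC and the within-person correlation. The trends reported for planning are more exposed than the training effect if data are pre/post only: at a 0.19 SD gap the spurious drift would be about 1.35×0.19 = 0.26 SD.

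A bias of a full standard error, or a threat to the pilot's main conclusions, is not supported: the first needs a trust gap that the article does not document, and the feasibility outcomes do not pass through this model.

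**What to change.** Make the Design item, the rollout text and the Randomisation item agree, and state what is randomised. There are two routes.

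1. **Randomise team order across both trusts, stratified so that both appear early and late.** With four FTB (F) and two second-trust (E) teams, F-E-F-F-E-F and F-F-E-E-F-F have zero leak in the pre/post layout. Unstratified randomisation averages zero, but a single draw can still reach ±0.225. The cost is that the second trust must be ready near the start of the rollout.
2. **If FTB has to start first, or the rollout is already done** (recruitment was due to end in January 2026), state that order was randomised within trust, if true, and add trust as a fixed effect in the CBMCS model. This removes the bias from a constant trust difference in every layout tried. The price is precision. At ICC 0.05 the SE rises from 0.104 to 0.152 SD (4+2 teams, pre/post, correlation 0.7), but only from 0.114 to 0.118 with complete data and correlation 0. The trust term does not protect against trends that differ between trusts, so that limitation should be stated beside the reported trends.

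### WP2 places exposure at the team's crossover but describes CBMCS follow-up only after training, so on a plain reading the outcome data cover completers only; uptake also has no stated window from crossover

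*Protocol article*

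**What the plan says.** **Exposure.** The WP2 Design paragraph describes "random and sequential crossover of clusters (youth mental health teams) from control to intervention (our e-learning module) until all clusters are exposed". The Control paragraph likewise separates an unexposed from an exposed observation period at the crossover. The Randomisation line adds: "Cross-over of clusters (clinical team; n=6) from control to intervention will occur approximately every 4 weeks". Exposure therefore belongs to the team and starts on a scheduled date.

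**CBMCS timing.** The Methods paragraph says: "Staff will complete the training outcome measure before and after the e-learning". The text under Figure 3 says: "Baseline (pre-training) and post-training (4 weeks later) data will be collected electronically via the NHS Learning Hub platform". The same platform hosts the module. The Outcome paragraph contrasts scores from before and after training to obtain mean change and ICCs. No CBMCS measurement is described for staff whose team has crossed over but who have not trained.

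**Uptake.** The Outcome paragraph lists "training uptake, defined as the proportion of eligible staff completing the e-learning module within each cluster" among the feasibility outcomes, beside acceptability. The definition gives no period. The Analysis paragraph will summarise uptake descriptively, by team and by step. Methods puts the rollout in months 4 to 9; the Figure 3 caption refers to "sequential rollout of the e-learning intervention across six clusters over the 12-month study period".

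**Use of the results.** The Analysis paragraph passes variability, ICCs and time trends to the sample size calculation of the definitive trial. WP4 makes incremental cost per unit improvement in multicultural competence part of its primary economic outcome.

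**The concern.** The design and the measurement schedule run on different clocks. In a stepped wedge a team counts as exposed from its crossover, whether or not each member takes the module. If the second CBMCS exists only for those who took it, the exposed period is represented by staff who selected themselves. Their mean change is not the change produced by offering the module to a team, and their variance and ICC need not match those of all staff in the team. A cluster trial planned on these values could expect too large a team-level effect, and the cost per unit of improvement in WP4 could look too favourable.

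Uptake has a related gap. Without a window from crossover, a team's figure can mix willingness to do the module with time available to do it. WP2's feasibility results are meant to inform progression, so what the percentage measures should be fixed.

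**Working it through.** **1. What the 4 weeks could run from**

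The protocol does not name the starting point. There are three candidates.

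- From the person's own training: only completers have a follow-up score.
- From the person's baseline: some scores labelled as post-training may come from people who have not trained.
- From the team's crossover: the same mislabelling arises, unless non-completers are surveyed and identified as such, which is not described.

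The first is the plain reading of the Methods sentence and the text under Figure 3. None of the three gives a follow-up score for all staff that is clearly tied to the exposed period.

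**2. Size of the completer effect**

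Let u be uptake and d the mean change among completers. If non-completers do not change (an assumption), the team-level change is u × d, so the completer figure is 1/u times the team-level figure. The protocol gives no value for u. Illustrations: u = 0.50 gives 2.00; u = 0.60 gives 1.67; u = 0.90 gives 1.11.

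**3. Access time under one common count**

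Inputs from the protocol: 6 teams, about 4 weeks between crossovers, rollout in months 4 to 9. The first and last crossovers are 5 × 4 = 20 weeks apart. If all teams are counted T weeks after the first crossover, team i has T − 4(i − 1) weeks of access.

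- Count at the end of month 9 (T about 26): 26, 22, 18, 14, 10 and 6 weeks; ratio 26/6 = 4.3.
- Count at the end of month 12 (T about 39): 39, 35, 31, 27, 23 and 19 weeks; ratio 39/19 = 2.1.

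**4. What that could do to uptake**

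Assume the same constant weekly completion rate r in every team, so that teams do not truly differ. Expected uptake after w weeks is 1 − exp(−r × w). For example, at r = 0.10 and a month-9 count, 1 − exp(−2.6) = 0.93 for the first team and 1 − exp(−0.6) = 0.45 for the last.

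| Assumed r per week | Month-9 count, first to last team | Month-12 count, first to last team | Fixed 4-week window, every team |
|---|---|---|---|
| 0.05 | 73% to 26% | 86% to 61% | 18% |
| 0.10 | 93% to 45% | 98% to 85% | 33% |
| 0.20 | 99% to 70% | 100% to 98% | 55% |

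For scale, 120 staff over 6 teams is 20 per team. The 95% half-width of one team's uptake at 50% is 1.96 × √(0.5 × 0.5/20) = 0.22, or 22 points. At r = 0.10 the month-9 gap of 48 points is well above that, and the month-12 gap of 13 points is below it. The 20 per team is itself only indicative, because the number of eligible staff in each team is not given.

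The protocol has no uptake target, window or CBMCS effect to reproduce. Its 120 rests on general recommendations for pilot studies, not on a formula.

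**The case against.** **The protocol already places exposure at the team.** This is correct. A reader might infer that WP2 counts exposure from each person's own completion; the Design and Control paragraphs say otherwise. The problem is the mismatch between that definition and the measurement schedule.

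**Completer-only follow-up is never stated.** Also correct: it is the plain reading, not an express rule. A condensed article may leave the anchor of the 4 weeks and the uptake cut-off to a fuller document. That weakens the uptake point more than the CBMCS point. A later analysis plan can add a window if completion dates were recorded, but it cannot recover scores that were never collected.

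**Uptake by team and step is already planned.** This is a partial answer. Such tables may allow comparison at equal time since crossover, but the definition itself does not ask for it. Unequal access also needs a common counting date, which is not stated.

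**The trusts.** A reader might infer that teams in the first trust will look better on uptake for timing reasons alone. The protocol does not support that. Four teams from month 4 at 4-week steps reach roughly month 7, and the second trust runs from month 6 to month 9, so the two overlap. Nor does the protocol rank uptake as the lead outcome or plan a comparison between trusts.

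**It is a pilot with no test of effectiveness.** True, and this limits the consequence. Supplying variance and ICC values for the next trial is nevertheless a stated purpose, so the population they describe matters.

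**Conclusion.** The point holds in limited form. Exposure is defined by team crossover, while the only CBMCS follow-up described is tied to training. On the plain reading, non-completers in crossed-over teams are not followed, and the estimates carried forward are completer estimates. Their excess over the team-level change is a factor of 1/u if non-completers do not change; u is unknown.

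The uptake part is weaker. The definition has no window from crossover, and a common count would give a 20-week difference in access between the first and last team. How much that moves uptake depends on an assumed completion rate and end date: at 0.10 per week, by 48 points at month 9 and 13 points at month 12. It could be almost nothing if completion is quick and counting is late. This is a change that should be made, not a fault that invalidates the pilot.

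**What to change.** - **CBMCS.** Send the follow-up to every staff member with a baseline at one fixed time after the team's crossover, whether or not the module was completed. Summarise scores by the team's scheduled phase, and give completers as a secondary description.
- **Uptake.** Report the proportion of staff eligible at crossover who complete within the same fixed time since crossover in every team, for example one step of about 4 weeks. Show later completions separately. With the last crossover at week 20, a 4-week window closes at week 24, inside the roughly 26-week rollout.
- **If it is too late to follow non-completers.** Trial status says recruitment was due to end in January 2026. In that case label the CBMCS results as completer-only, including where they feed the definitive trial and WP4, and derive fixed-window uptake from completion dates if these were recorded.

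**Cost.** Protocol wording and survey invitations to staff already enrolled. Headline uptake and CBMCS change will probably be less favourable, and response among non-completers may be low, so response should be reported separately for completers and non-completers.
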